## Abstract

**Background:**

The rising prevalence of type 2 diabetes underlines the importance of secondary strategies for the prevention of target organ damage. While access to diabetes education centers and diabetes intensification management has been shown to improve blood glucose control, these services are not available to all that require them, particularly in rural and northern areas. The provision of these services through the Home Care team is an advance that can overcome these barriers. Transfer of blood glucose data electronically from the home to the health care provider may improve diabetes management.

**Methods and design:**

The study population will consist of patients with type 2 diabetes with uncontrolled A1c levels living on reserve in the Battlefords region of Saskatchewan, Canada. This pilot study will take place over three phases. In the first phase over three months the impact of the introduction of the Bluetooth enabled glucose monitor will be assessed. In the second phase over three months, the development of guidelines based treatment algorithms for diabetes intensification will be completed. In the third phase lasting 18 months, study subjects will have diabetes intensification according to the algorithms developed.

**Discussion:**

The first phase will determine if the use of the Bluetooth enabled blood glucose devices which can transmit results electronically will lead to changes in A1c levels. It will also determine the feasibility of recruiting subjects to use this technology. The rest of the Diabetes Risk Evaluation and Management Tele-monitoring (DreamTel) study will determine if the delivery of a diabetes intensification management program by the Home Care team supported by the Bluetooth enabled glucose meters leads to improvements in diabetes management.

**Trial Registration:**

Protocol NCT00325624

## Background

### Diabetes and its impact on the community

Diabetes is a systemic disorder resulting in abnormally high blood glucose levels. These elevated levels impact directly and indirectly on every part of the body. Diabetes is the number one cause of end stage renal disease (ESRD), preventable blindness, as well as a major cause of premature heart disease, stroke, limb amputation and preventable hospital admissions[1]. Prevention of type 2 diabetes through primary control programs is society's ultimate goal but current evidence indicates that this goal is failing as rates of diabetes are rising rapidly. For example in the Province of Ontario, prevalence rates of diabetes rose by 69% to 8.8% in the 10 year period ending 2005[2]. Secondary prevention strategies to help reduce the complication rate in this burgeoning population of people with diabetes are desperately needed. Control of blood glucose levels prevents new microvascular disease and has recently been shown to have a legacy effect and is a central focus of diabetes management programs[3], in addition to the significant health benefits of blood pressure and lipid control. The optimal degree of blood glucose normalization has recently come into question. While the ADVANCE study demonstrated a reduction of microvascular but no significant reduction of macrovascular events with normalization of A1c to below 7.0%[4], the ACCORD study, also targeting normalization of A1c below 7.0%, found an elevated mortality and no reduction of cardiovascular events[5].

For those who develop diabetes, control of blood glucose is important to prevent new microvascular target organ damage. Blood pressure control prevents both micro and macrovascular damage and lipid control macrovascular changes. Two examples of health care initiatives to control blood glucose levels in people with diabetes are now the standard of care: The development and wide dissemination of the Canadian Diabetes Association's Clinical Practice Guidelines[1] and the widespread dissemination of Diabetes Education and self-management[6]. The guidelines are evidence based and described in detail and, if followed, would lead to control of blood glucose levels. The guidelines are largely based on outcomes research carried out in carefully controlled settings. The challenge is in implementing them in a real world setting. Diabetes education centers and Diabetes Educators are a necessary part of the team for intensive diabetes management[6], but are still not accessible to many people living in rural and Northern areas. Furthermore there are only a few Diabetes Education Centers designed specifically for First Nations peoples. The closest in 2007 for the people living in Northern Saskatchewan where this study takes place, is more than a 3 hour drive away in Edmonton. However, Home Care teams which provide home visits from nurses and even dietitians and other members of the multidisciplinary team are able to access virtually all communities. Traditionally Home Care teams have provided wound and dressing care. However, the Home Care team can include Diabetes Educators that can deliver evidence based therapy as part of a chronic disease management program for diabetes.

We believe that this study protocol has relevance with respect to the development of a new community-based approach to the control of blood glucose. We have recently demonstrated that the Home Care team (which provides supportive care provided in the patient's home by healthcare professionals) of the Battlefords Tribal Council Indian Health Services, can improve blood pressure control using a chronic disease management model for multiple drug therapy[7]. We believe that a chronic disease management model linking the Home Care Team including Diabetes Educators[6] with their clients and the primary care providers to try to bring A1c to 7.0% can improve blood glucose control safely. Combining elements of chronic disease management including provider education, patient education, clinical practice guidelines, decision support and disease measurement is expected to lead to lasting improvements in diabetes management[8]. Use of the Bluetooth enabled glucose meters may be able to enable diabetes intensification in a safe and effective manner, allowing the Home Care team to review their clients with access to their client's self monitored blood glucose results.

### Diabetes, First Nations and kidney disease

End stage kidney disease (ESRD) comprises an enormous public health burden, with an incidence and prevalence that are increasing alarmingly. For example, between 1998 and 2002, the prevalence of ESRD in Canada increased 33%, while the incidence increased 17%[9]. In Canada, 4.7% of all new dialysis starts are identified as Aboriginal while in the province of Saskatchewan 19.7% of new dialysis starts are identified as aboriginal[10]. In a study of the aboriginal population of Australia, Hoy found an incidence of ESRD in this population ten times greater than the incidence in the general population [11]. First Nations Peoples are at higher risk for ESRD, largely due to diabetes [12-15]. The prevalence of diabetic nephropathy is much higher among Aboriginal Canadians than in the general population, with rates ranging from 25–60%[16,17]. Morrison [18] noted that in the First Nations population of the Sioux Lookout Zone, Northwestern Ontario, that children as young as five years of age have been diagnosed with type 2 diabetes. With diabetes occurring at increasingly younger ages, ESRD is going to become more prevalent in a younger age group with diabetes[16]. Canada is not alone in this respect as the prevalence of kidney disease in the Australian Aboriginal population with diabetes is approaching 50%[19,20]. Hypertension in those with diabetes is a strong predictor of death from diabetic nephropathy [21]. The etiology of the diabetes epidemic in the aboriginal community is multifactorial in nature, including social and societal issues endemic to Western society and those specific to the aboriginal community, as well as genetic factors and are beyond the scope of this project [22].

Unless early and sustained blood glucose control can be achieved, higher rates of diabetes with earlier age of onset will result in more frequent complications from diabetes with resultant higher costs to quality of life and the health care system. Linked to the rising rates of diabetes in Aboriginals are risk factors for and higher rates of cardiovascular disease [23-32]. Kidney disease, now recognized as a significant marker of cardiovascular disease [33-35], may be in part responsible for this and blood glucose control has been demonstrated to be effective in reducing the progression of kidney disease in the setting of diabetes[36]. However, medication alone is insufficient to achieve control. London[37] has demonstrated, in an Australian Aboriginal diabetes study, that health information must also incorporate the contemporary beliefs of the community. Implementation of treatment programs with First Nations peoples must be carried out with sensitivity to cultural mores and beliefs [38-42].

Intensification of Diabetes Management. The current Canadian Diabetes Association Clinical Practice Guidelines recommend similar glycaemic goals for both type 1 and type 2 diabetes and define optimal glycaemic control as an A1c < 7.0% [43]. A stepwise approach is advocated with initial therapy consisting of lifestyle changes followed by the addition of one or more oral hypoglycemic agents, followed by the addition of/replacement by insulin. Given that diabetes is a progressive disease, the need for insulin in people with type 2 diabetes, will continue to rise. A team approach is also recommended; the person with diabetes is at the core of this team with the primary care physician, diabetes nurse educator, dietitian, diabetes and other specialists, and others also being members. The CDA Clinical Practice Guidelines recommend a A1c < 7.0%. Although A1c is considered to be the best measure of overall glycaemic control, blood or capillary glucose levels are still important to obtain in order to safely and effectively manage the doses of the oral hypoglycemic agents and insulin. This can best be done by having the person with diabetes perform self-monitoring of blood glucose (SMBG) at various times of the day.

There is now evidence in both type 1 as well as type 2 diabetes that improved glycaemic control will reduce the microvascular complications of diabetes[44]. An epidemiologic analysis of the UKPDS[45] showed that there is no threshold for benefit when it comes to glucose lowering, and that any reduction in A1c is associated with reduced risks for both micro- and macrovascular disease. In their analysis, every 1% decrease in A1c was associated with a 25% reduction in risk for myocardial infarction[45]. The ADVANCE study demonstrated a reduction of microvascular events with normalization of A1c to below 7.0%[4]. The ACCORD study which targeting aggressive normalization of A1c in patients with longstanding diabetes, found an elevated mortality in the intensive group which targeted normalization of blood gluocse[5]. The goal of diabetes intensification in this study is to reduce the risk for the complications of diabetes by controlling blood glucose safely.

### Rates of use of insulin and hypoglycemia, evidence from clinical trials

Studies of glycaemic control in people with type 1[46] and type 2[44] diabetes have shown improvements in complications such as the progression of kidney, eye and heart disease. Achieving control of blood glucose requires adherence to lifestyle changes as well as titration of medications, including the initiation of insulin therapy and the titration of the insulin dose. The intensive treatment group of the STENO-2 study led to over 50% being started on insulin with an average dose of 62 units per day[47]. Of interest, a greater proportion of the usual care group was started on insulin and there was a trend to higher doses. The glycaemic target in the intensive arm of the STENO-2 study was an A1c of 6.5%, compared to about 7.5% in the control arm. Despite lower blood glucose levels attained in the intensive treatment group, there were fewer major hypoglycemic complications (eg. impaired consciousness which required help from another person) in the intensive treatment compared to the control group (just under 1% vs. 2% per patient year respectively)[47]. In the UKPDS 33 study the rates of major hypoglycemic episodes per year were also relatively low, 0.7% with conventional treatment, 1.0% with chlorpropamide, 1.4% with glibenclamide, and 1.8% with insulin[48,49]. Fear of the complications of insulin therapy, particularly hypoglycemia, by both patients and health care workers, is one of the major barriers to implementing intensification of diabetes management. The ability to monitor blood glucose levels remotely in people who are having their diabetes medications adjusted may go a long way to providing the same kind of safety net for diabetes management that was the rationale for managing diabetes in the hospital setting years ago.

### The Battlefords Tribal Council Indian Health Services and approach to diabetes

The Battlefords Tribal Council Indian Health Services is a First Nations owned and operated Health Services organization established over 26 years ago. The Board of Directors consists of the seven Chiefs of the Battlefords Tribal Council First Nations. The population of each of the seven communities ranges from 500 to 700 people for a total population of 4,121 persons living on reserve[50]. North Battleford serves as the central base for the delivery of health services for the seven communities. All communities are within 90 kilometers of medical facilities. The culture is primarily Cree, and Cree and English languages predominate. A survey completed in 1999 found that diabetes, heart disease, cancer and high blood pressure were the top four most serious health-related problems for the community[50]. Diabetes was found in 22% of adults[51].

The Home and Community Care Diabetes Education Program has a ten year history and has been constantly evolving during that time. The Program encompasses all levels of prevention: primary, secondary and tertiary. Program staff includes one Home Health Aide and Registered Home Care Nurse in each community. A dietitian, diabetes nurse educators and exercise therapist serve all communities. Four of the staff members (1 dietitian and 3 nurses) have received Canadian certification as Diabetes Educators. All program development considers cultural appropriateness; in addition, nine staff members are fluent in the Cree language.

The Home Care team has always had a primary prevention component and this has been significantly augmented in the last three years through the Aboriginal Diabetes Initiative that has helped to increase community access to fresh fruits and vegetables through a Good Food Box program; a granting process to support community-based initiatives (walking groups, healthy snacks, cooking groups); a training program for staff who cook meals in the schools; and, a healthy lifestyles newsletter. Secondary prevention is addressed through diabetes education provided to people with diabetes and members of their family. Another component of client education is foot assessment and care; nurses hold regular foot care clinics. Prior to the DreamTel program, the Home Care team did not provide diabetes treatment or management. Instead, staff members referred clients to their family physician and advocated for treatment, with referral to specialists as needed. Prior to the DreamTel program, for the initiation of insulin in community members with type 2 diabetes, it was standard practice for primary care providers to arrange for admission to hospital for insulin initiation. Diabetes intensification was coordinated through the Diabetes Education Center at the Battlefords Hospital. However, its distance from people living on reserve with diabetes limited their access for repeated visits and ongoing education and treatment. At the time the DreamTel program was initiated, there were no diabetes specialists in Northern Saskatchewan, so that there was no backup for primary care providers. All of this added to the risk for clinical inertia for diabetes intensification and the initiation of insulin.

The ability to accurately monitor blood glucose results with self monitoring of blood glucose (SMBG) is pivotal to the success of managing and controlling blood glucose levels in people with diabetes on insulin. Glucose meters in current use require the user to record the displayed result into a logbook along with the timing of the reading. This allows cumulative readings to be analyzed for patterns. Barriers to health care workers receiving accurate logbooks include the ability and willingness of the person using the glucose meter to record the results accurately and to bring the logbook with them to appointments with health care providers. Evidence provided by glucose meters with memories has demonstrated that the recording of results into logbooks may not be accurate[52], even when glucose meters users know that their device is also recording the levels. Furthermore, health care providers only get access to the information in the logbook or that stored within the glucose meter during patient or client visits. This may lead to prolonged episodes of dysglycaemia before the client can receive medical attention. Bluetooth enabled glucose meters facilitate the downloading of the results to a secure electronic format available to health care providers via a web interface. This may help to eliminate the effects of geography and will allow the potential for more frequent health care monitoring of SMBG. The health care team can arrange for more frequent monitoring during titrations of drug therapies or the initiation of insulin. Patients with questions about their management will be able to initiate a health care provider review of their results by phone-call without generating a visit.

The ultimate goal of the DreamTel project is to develop a process for initiating insulin therapy in the community setting including intensification of diabetes management in a culturally appropriate manner. If successful, the legacy of the project will be a change in medical practice in the community with the introduction of a chronic disease management model for type 2 diabetes management, where primary care physicians can consult with the Home and Community Care team for initiation of insulin therapy in the community as well as intensification of diabetes therapy.

## Methods and design

The DreamTel project is designed to be carried out in 3 phases. In the first phase, the new technology will be introduced to volunteer subjects with uncontrolled type 2 diabetes. The second phase includes the development and implementation of a nurse directed medical management model for type 2 diabetes to allow a change in practice within the community. The goal is to allow primary care physicians in the community to refer patients to the Home Care team for initiation of insulin and diabetes intensification. This process involves health care provider education, the development of algorithm driven protocols based on clinical practice guidelines, patient education and disease measurement. In the third and final phase, subjects from the first phase who successfully used the device 80% of the time will be invited to participate in diabetes intensification with oversight from their primary care physicians.

### Phase 1: Introduce the Bluetooth-enabled glucose meters into the community

Experimental Design. The target populations for the DreamTel study are participants with Type 2 diabetes and uncontrolled blood glucose levels with A1c levels in excess of 7.0%. Fifty subjects are targeted in the pilot study. Clients willing to participate in the program who have uncontrolled diabetes based on A1c levels above target will receive information on the use of the Bluetooth enabled device and will be consented into the project. They will then have the device installed into their home and receive training on its use from the Home Care team. Technical support is available from the sponsor. For the first phase, lab testing for A1c takes place at initiation of the device and after three months. Subjects will be identified by their primary care physician or by the Home Care team as needing diabetes intensification. Thus they will constitute a convenience sample. Subjects will be trained in the use of the glucose meters but do not have to be taking insulin on enrollment. All will be trained on the Bluetooth technology. The LifeStat service is an Integrated Communications Technology to capture physiological data that is transmitted via Bluetooth to an aggregation device located at the point of care. The aggregation device can be a cell phone but in the DreamTel study due to insufficient local coverage a Bluetooth/Analog modem with the local telephone will be used. The data is then forwarded to a secure hosting center by standard telephone network. The information is then accessed by users with the appropriate credentials through a care giver portal.

All subjects receiving the device will have a multi-disciplinary team diabetes assessment with standard diabetes screening tests including a baseline A1c level and agree to follow-up lab work on a three-month basis throughout the duration of the study. Each study subject will receive training in how to use the device and will be instructed on how to indicate that a test run was a validation test or another person's sample. Subjects will be instructed to use the results of the testing to manage their diabetes according to the education they received in light of food intake (or lack of), physical activity and whether medication had been taken. The client will be taught how to use the device and how to demonstrate that they were able to accurately use it. Data forwarded to the web server will be displayed through the portal graphically and include summary statistics. Data can also be printed by the patient's health care providers and could became part of the client's medical record. All consenting subjects will be asked to notify their primary care physicians that they are using the new device during regularly scheduled visits. Their physicians will also receive information packages from the Home Care team on the study and will be invited to participate in local Continuing Health Education programs on the study and the technology used. To determine whether the installation of the LifeStat device linked to the patient's telephone line impacts on blood glucose control, the A1c level at baseline (prior to its installation) will be compared to the three-month value. Typically A1c levels remain stable over short periods of time, rising over a period of years[45].

To provide data on whether the blood glucose monitoring was before or after a meal, a teleprompt will be delivered to the client's phone. When a blood glucose result is received by the central server at SaskTel's central office in Saskatoon, Saskatchewan, an automatic teleprompt will call requesting a response as to the relationship between the test result and the last food intake. The teleprompt was developed in English and in Cree. Patients will be trained in its use. Each patient's impression of the teleprompt system will be addressed in questionnaires administered after the first 3 months of its use. Learning challenges will be collected as qualitative data to record the duration of time spent teaching and to record the challenges faced.

Another objective for the first three months of use is to compare data from three different sources; data transmitted by the device and stored on the web site, data stored on the device itself and the patient's log book, noting discordant values. Data is to be presented as the proportion of results recorded accurately. The frequency of monitoring based on data from the electronic output is to be assessed for the entire period.

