### Inclusion criteria

Type 2 Diabetes with baseline A1c ≥ 7.0% on diet or medical therapy with no history of diabetic ketoacidosis. Patients must be greater than or equal to 18 years of age. Written informed consent must be obtained prior to admission to this study.

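### Phase 1 credits the three-month A1c change to the device, but selection on high A1c and concurrent team input can also produce a fall; the qualifying and baseline A1c values need separating and the aim restating

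*Protocol article*

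**What the plan says.** The Phase 1 section gives a causal aim: "To determine whether the installation of the LifeStat device linked to the patient's telephone line impacts on blood glucose control". The means is that "the A1c level at baseline (prior to its installation) will be compared to the three-month value". The Discussion part of the abstract repeats the attribution, in a sentence that begins "The first phase will determine if the use of the Bluetooth enabled blood glucose devices" and goes on to name A1c as what the device may change. The one supporting argument, in the Phase 1 section, is "Typically A1c levels remain stable over short periods of time, rising over a period of years".

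On selection, the same section says "Subjects will be identified by their primary care physician or by the Home Care team as needing diabetes intensification", and describes the target population as uncontrolled, with A1c above 7.0%. It schedules two Phase 1 A1c tests, at device initiation and at three months. The Inclusion criteria section requires "Type 2 Diabetes with baseline A1c ≥ 7.0% on diet or medical therapy".

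On what else happens, the Phase 1 section states "All subjects receiving the device will have a multi-disciplinary team diabetes assessment". Patients are told to manage their diabetes from their readings in the light of education received, and their physicians are sent information packages and invited to education sessions. No Phase 1 group receives these without the device. The control group mentioned under Phase 2 consists of patients whose physician declines intensification by the Home Care team, so it does not serve Phase 1.

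**The concern.** Short-term stability of A1c is a statement about drift in an unselected group. It does not protect a group admitted because A1c was high. If the value that qualifies a patient is also the before value, part of it is chance elevation, and the follow-up mean is expected to be lower even if nothing is done. Separately, the team assessment, the instruction to act on results and the physician information all accompany the device, so a genuine fall could come from any of them.

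At stake is the Phase 1 statement about the device. A fall in A1c is the likely finding whether or not the device works, and the article says that this phase will determine the device's effect.

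**Working it through.** The article gives no SD, correlation, test or expected change for this comparison, so there is no stated figure to reproduce. The check asks what the comparison shows when the device does nothing.

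**Inputs from the article.** n = 50 (Phase 1 section); cutoff 7.0% (Inclusion criteria); 45% of subjects at or above 8.0% in the earlier DREAM3 study (Phase 3 section), used to place the mean.

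**Assumptions.** Normal A1c; SD 1.3 to 1.9; correlation ρ between A1c values three months apart of 0.7 to 0.9; two-sided 5% paired t-test; all 50 patients measured twice.

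**Formulas, baseline alone qualifies.**
- Mean: μ = 8.0 − 0.126 × SD
- Standardised cutoff: c = (7.0 − μ)/SD, and λ = φ(c)/(1 − Φ(c))
- Expected fall with no effect = (1 − ρ) × SD × λ
- SD of change = SD × √[(1 − ρ²) + (1 − ρ)²(1 + cλ − λ²)]
- Rejection rate from the noncentral t distribution, 49 degrees of freedom

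**Worked case, SD 1.6, ρ 0.8.** μ = 7.80; c = −0.50; λ = 0.51. Fall = 0.2 × 1.6 × 0.51 = 0.16. SD of change = 1.6 × √(0.36 + 0.04 × 0.486) = 0.99. Noncentrality = 0.163/(0.986/√50) = 1.17. Rejection is 21%, almost all of it in the direction of benefit, where the nominal rate is 2.5%.

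**Three readings of the eligibility rule.** The second and third rows are from simulation, with the same correlation between any two A1c values.

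| Which A1c must be ≥ 7.0% | Spurious fall | Rejection | SD 1.6, ρ 0.8 |
|---|---|---|---|
| Baseline only | 0.06 to 0.32 | 11% to 35% | 0.16; 21% |
| Earlier value and baseline | 0.03 to 0.22 | 7% to 19% | 0.11; 12% |
| Earlier value only | 0.00 | about 5% | 0.00; about 5% |

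Separate simulation runs agree within about two percentage points (upper ends 0.33 and 37% in the first row, 18% in the second). The zero in the last row depends on the equal-correlation assumption. If correlation weakens as the gap lengthens, some fall remains.

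**Co-intervention.** Suppose, purely for illustration, that assessment and instruction lower A1c by 0.2 points and the device does nothing. Over SD 1.2 to 2.0 and ρ 0.7 to 0.9, a significant fall appears in about 68% to 90% of trials if baseline alone qualifies, and still in about 14% to 75% with a separate, unselected baseline. A clean baseline therefore does not isolate the device.

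**The case against.** The strongest reply is that the baseline may not be the qualifying value. The Phase 1 section describes a sequence: patients known to be above target are identified, informed and consented, then have the device installed, with A1c drawn at initiation. On that account an earlier clinical A1c prompts referral and the initiation draw is fresh. This stands as a real possibility. A reader might infer that baseline is certainly the sole qualifying value, but the documents do not settle it: the Inclusion criteria point one way and the Phase 1 sequence the other.

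A reader might also infer that all the diabetes education falls within the three months. The article gives no timing for it, and the Background describes a Home Care education programme with a ten-year history, so some may predate enrolment. What is tied to the study is the team assessment, the device training, the self-management instruction and the physician information. Training and use of readings could fairly be called part of introducing the device; the assessment and the physician information less so.

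The inputs are also partly assumed. DREAM3 is cited as a blood pressure study, so its A1c distribution is only a rough anchor.

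Finally, little else depends on this comparison. The primary outcome is A1c at six months, entry to Phase 3 turns on 80% testing adherence and willingness, and the closing Discussion admits the pilot design and convenience sample. That lowers the priority. It does not answer the point, because those limitations mention neither selection on a high value nor co-intervention, and the claim to determine the device's effect remains.

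**Conclusion.** The attribution of the Phase 1 A1c change to the device is not supported as written, and it should be fixed. The co-intervention part holds under every reading of the eligibility rule, though its size is unknown. The regression part depends on which A1c qualifies: about 0.06 to 0.32 points with 11% to 35% rejection if baseline alone counts, about 0.03 to 0.22 with 7% to 19% if both values count, and essentially nothing if only an earlier value counts. These ranges rest on the assumed SD, correlation, normality and test. Where the baseline value must reach the cutoff, the spurious change is always a fall.

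One could go further and say that the same bias enters the Phase 3 result. The documents do not establish this. It would follow only if the pre-device A1c were reused as the Phase 3 baseline, and the article does not say which value is used. Nor does the point undermine the feasibility, adherence or data-concordance aims of Phase 1.

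**What to change.** 1. Reconcile the Phase 1 section with the Inclusion criteria. State that the patient qualifies on an A1c already on file, that the separate draw at device initiation is the analysis baseline, and that all enrolled patients are analysed whatever that second value is. Use the same cutoff wording in both places; one now says above 7.0% and the other at or above.
2. Extract earlier A1c values from the charts and report them as the pre-device trend. This also shows whether values were already falling before installation.
3. In the abstract and the Phase 1 section, restate the aim as the A1c change after the device together with team assessment and instruction, and drop the claim that Phase 1 will determine the device's effect.

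The cost is some chart extraction, a change to the eligibility wording, a few patients with baseline below 7.0%, and a smaller visible change. No new visits or arms are needed. The separate baseline deals with regression to the mean only. The co-intervention problem is met by the restated aim, since separating out the device would need a concurrent group given the same assessment and instruction.
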